### Patient pathway

The pathway is outlined in Figures 1, 2 and 3.

**Figure 2 Fig2:**
[figure not shown]
Patient pathway.

**Figure 3 Fig3:**
[figure not shown]
Protocol for medical management of cardiovascular risk factors in patients randomised to CR group.

### Informed consent

Patients will be identified and given information about the trial from three settings and seen by the local Principal Investigator, a Research Investigator or the Lead CR Nurse:At the surgical outpatient clinic when it is certain that aortic aneurysm repair will be scheduled. The trial will be discussed with the patient and the patient given a Patient Information Sheet.At the pre-operative assessment clinic.On admission for surgery, prior to aortic aneurysm repair.

Formal written consent will be obtained after the patient has undergone aortic aneurysm repair and been deemed fit for discharge from hospital.

### Randomisation

After informed consent has been obtained, a nominated research investigator will randomise the patient using a secure online NIHR-accredited Clinical Trials Unit Randomisation Service (King’s Clinical Trials Unit). The patient will be allocated a unique trial identification PIN number. Neither investigators nor patients will be blinded to treatment allocation. The patient’s GP will be notified of the treatment allocation, and supplied with a reminder letter highlighting current NICE guidelines for the medical management of cardiovascular risk in patients with peripheral vascular disease.

### Treatment and follow-up

Patients randomised to CR will be seen by a member of the Cardiac Rehabilitation team on the ward prior to discharge if possible, or at the induction CR meeting scheduled 4–6 weeks after aortic aneurysm repair. The CR Arm will receive a protocolised approach to intensive medical risk factor reduction (Figure 3) in addition to enrolment in the local multimodal Cardiac Rehabilitation programme, which should follow national guidelines (www.cardiacrehabilitation.org.uk). CR is an existing national service, comprising a protocolised 8–12 week regime of supervised exercise, lifestyle modification, dietary interventions, psychological assessment and medical risk modification. Each weekly session takes 1 to 2 h and is supervised by two nurses trained in CR, two qualified physiotherapists and one occupational therapy technician. Patients assessed as being low-risk attend sessions with a maximum of 20 patients; those deemed high-risk attend sessions with 12 patients. Each session begins with a “check-in” consisting of a blood pressure and heart rate check and a review of each patient’s progress to date. The group then proceed through a supervised warm-up of 10–15 min, followed by the main exercise session of 45 min. This is followed by a warm-down, and finally a “check-out” consisting of further blood pressure and heart rate measurement.

An individual assessment is made of each patient’s progress and needs; in some cases this involves extending the duration of the patient’s participation in the programme beyond the initial 8 weeks. The patients that have been randomised to “treatment as usual” will receive “standard” follow-up, i.e. routine post-operative out-patient appointments and/or follow-up scans as necessary and GP-based management of their co-existing co-morbidities such as hypertension. Local standards for routine outpatient care after A/TAA repair will be unaffected by the trial, including existing appointments for endograft surveillance and vascular surgery outpatient review.

Patients in both arms of the study will undergo blood tests, urinalysis, salivary testing, biometric assessment and quality-of-life assessment at 6 weeks after surgery (entry to CR in the CR group) (Figure 2). These tests will be repeated, in addition to follow-up echocardiography, in all patients at 12 weeks after randomisation to CR (or 12 weeks after surgery for those randomised to standard care) and 6 months after randomisation into CR (or 6 months after surgery for “standard care” patients).Blood tests will comprise hsCRP, troponin, BNP, lipid profile, fibrinogen, urate, eGFR, HBA1C and serum insulin.Patients who smoke will have salivary cotinine testing conducted and breath carbon monoxide testing on entry to CR (or 6 weeks after randomisation in the standard care group), 12-weeks after randomisation to CR and at 6-month follow-up.

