### Secondary outcome measures

Time to death.Time to first adverse cardiovascular event after aneurysm repair.The composite “adverse cardiovascular event” outcome includes: non-fatal myocardial infarction, stroke, non-traumatic amputation and revascularisation. The revascularisation endpoint comprises strictly defined coronary procedures (coronary artery bypass graft surgery, percutaneous coronary interventions and percutaneous coronary interventions) and peripheral vascular procedures (embolectomy, bypass and angioplasty). In the absence of relevant COMET outcomes (www.comet-initiative.org), this outcome measure mirrors the composite cardiovascular endpoint measured for previous randomised RCTs of cardiovascular risk reduction [14]. Analysis of the “composite cardiovascular disease event” endpoint will be adjusted to account for “competing risks”, for example, the intervention reducing the risk of one event but increasing the risk of another [15]. Outcomes will be compared with the BHF-funded National Audit of CR for attendance, adherence, and outcomes with MI, PCI and CABG patients.Intermediate phenotypic markers of cardiovascular risk measured at enrolment, 12-weeks after randomisation to CR and 6-months after randomisation to CR or standard care: serum lipids (total cholesterol, HDL and LDL), systolic and diastolic blood pressure, HbA1C, BNP, troponin, hsCRP, fibrinogen, homocysteine, urate, eGFR, serum insulin levels and echocardiographic measures of cardiac function. We will also be testing for urinary microalbuminuria at each time point.Indicators of patient behaviour and lifestyle, and patient biometrics, including: waist:hip ratio, waist circumference, BMI, ankle-brachial pressure index (ABPI) and toe pressures. Smoking cessation outcomes will include: salivary cotinine, expiratory carbon monoxide (<10 ppm), “prolonged abstinence” [16] and attendance at NHS stop-smoking services. Physical activity levels will be assessed by a 7-day-recall interview [17].Changes in patients’ attitudes to cardiovascular risk and their knowledge of their condition.Quality of life: EQ5D5L questionnaires will be administered at baseline, enrolment, 12-weeks after randomisation to CR or standard care and 6 months after randomisation to CR or standard care.Cost-effectiveness: Mean costs and quality adjusted life years will be compared on an intention-to-treat basis. The perspective will be the NHS and PSS. The analysis will include hospital re-admissions and pharmaceuticals. Unit cost will be obtained from the published literature.

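### The 12-week and 6-month assessments run from different time origins in the two arms, and this contradicts the schedule given under Secondary outcome measures

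*Protocol article*

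**What the plan says.** All references are to the protocol article.

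- **Treatment and follow-up, 12 weeks:** "12 weeks after randomisation to CR (or 12 weeks after surgery for those randomised to standard care".
- **Treatment and follow-up, 6 months:** "6 months after randomisation into CR (or 6 months after surgery for “standard care” patients".
- **Treatment and follow-up, first general assessment:** one rule for both arms, "at 6 weeks after surgery (entry to CR in the CR group".
- **Treatment and follow-up, first cotinine and carbon monoxide test in smokers:** "on entry to CR (or 6 weeks after randomisation in the standard care group".
- **Secondary outcome measures, phenotypic markers (after a measurement at enrolment):** "12-weeks after randomisation to CR and 6-months after randomisation to CR or standard care". The 6-month time applies to both arms; the 12-week time is given for CR only.
- **Secondary outcome measures, EQ5D5L:** "12-weeks after randomisation to CR or standard care and 6 months after randomisation to CR or standard care".

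The order of events is clear. Informed consent states: "Formal written consent will be obtained after the patient has undergone aortic aneurysm repair and been deemed fit for discharge from hospital". The Randomisation section under the patient pathway continues: "After informed consent has been obtained, a nominated research investigator will randomise the patient". The CR induction meeting is placed 4 to 6 weeks after repair.

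**The concern.** The time origin of an assessment should not depend on the allocated arm. Here it does: control visits are counted from the operation, and CR visits from an event that always comes after the operation. Randomisation cannot balance this difference, because the schedule assigns it together with the treatment.

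Estimating the effect of CR against standard care on risk markers, behaviour and biometrics, and quality of life is a stated secondary objective, and the pilot is meant to inform a definitive trial. Inflammatory and cardiac markers, physical activity and quality of life can plausibly still be changing in the months after aortic surgery. If so, a between-arm difference at 12 weeks mixes the effect of CR with the effect of a longer recovery. QALYs would inherit the mismatch if they are built from EQ5D5L scores collected on this schedule.

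There is also a practical problem. For quality of life at both visits and markers at 6 months, a site cannot follow both sections of the article, so the schedule used may vary between sites or staff.

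**Working it through.** There is no figure in the plan to reproduce. The check is date arithmetic after the rules are compared.

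**1. The rules side by side**

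| Assessment | Treatment and follow-up: CR / control | Secondary outcome measures: CR / control |
|---|---|---|
| EQ5D5L, 12 weeks | randomisation / surgery | randomisation / randomisation |
| EQ5D5L, 6 months | randomisation / surgery | randomisation / randomisation |
| Markers, 12 weeks | randomisation / surgery | randomisation / not given |
| Markers, 6 months | randomisation / surgery | randomisation / randomisation |
| First smoking test | entry to CR / 6 weeks from randomisation | not given |

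The control-arm origin conflicts in three of the four rows that concern EQ5D5L and markers. Salivary testing is also part of the general assessment at 6 weeks after surgery, so the first smoking test conflicts with a rule in its own section.

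**2. Time since surgery at each visit**

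Let g be the weeks from surgery to the CR-arm origin, and take 6 months as 26 weeks. Time since surgery is then 12 + g against 12 weeks, and 26 + g against 26 weeks. The documents do not give g, so two readings are shown.

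- *Literal randomisation, around discharge.* g is about the post-operative stay. Assume 2 to 14 days: g = 2/7 to 14/7 = 0.3 to 2.0 weeks.
  - 12-week visit: 12.3 to 14.0 against 12.0 weeks; g/12 = 2% to 17%.
  - 6-month visit: 26.3 to 28.0 against 26.0 weeks; g/26 = 1% to 8%.
- *Entry to CR, at the induction meeting.* g = 4 to 6 weeks.
  - 12-week visit: 16 to 18 against 12 weeks; g/12 = 33% to 50%.
  - 6-month visit: 30 to 32 against 26 weeks; g/26 = 15% to 23%.

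**3. Change from the 6-week assessment**

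That assessment is at 6 weeks after surgery in both arms. The interval to the 12-week visit is 12 − 6 = 6 weeks in controls and (12 + g) − 6 = 6 + g in the CR arm: 6.3 to 8 weeks on the literal reading, 10 to 12 weeks on the entry-to-CR reading.

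**4. First smoking test**

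For controls, 6 weeks after randomisation is 6.3 to 8 weeks after surgery, with the same assumed stay. CR patients are tested at entry, 4 to 6 weeks after surgery. Here the controls are later, by 6.3 − 6 = 0.3 up to 8 − 4 = 4 weeks.

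**5. What a timing bias could do (illustration only)**

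With 84 patients at 1:1, n = 42 per arm and the standard error of a standardised difference is √(2/42) = 0.218. For a timing bias of d SD and no treatment effect, the two-sided 5% test rejects with probability 1 − Φ(1.96 − d/0.218) + Φ(−1.96 − d/0.218). For d = 0.1, 0.2 and 0.3 this gives about 7%, 15% and 28%. The values of d are assumed; the documents give no recovery gradient for any marker.

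**6. With one common origin** the systematic gap at the 12-week and 6-month visits is 0 weeks in expectation, whatever the length of stay.

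**The case against.** The strongest reply concerns scope and size, and much of it stands.

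- **Not every secondary comparison is affected.** A reader might infer that all of them are confounded with time since surgery. The article does not support that. Time to first cardiovascular event is counted from repair with no difference by arm, time to death is not tied to these visits, and the general 6-week assessment has the same origin in both arms.
- **Event follow-up and cost windows.** A reader might also infer that these cover different periods by arm. The article states no arm-specific start or end for either, so that cannot be claimed.
- **The 4 to 6 week gap is one reading.** Treatment and follow-up uses both entry to CR and randomisation to CR, apparently for different events. Taken at its word, the rule gives a gap of about the hospital stay, which may be only days.
- **No bias has been shown.** The article gives no rate of change for any marker over this period, so neither the size nor the direction of a bias follows from it. It also does not say why a few weeks would alter biochemically measured smoking status.
- **This is a pilot.** The primary outcomes are enrolment and attendance within the CR arm, and the sample size rests on enrolment alone. The patient pathway figure could not be seen and may be clearer.

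The core is not answered. The two sections give incompatible rules for the same assessments, and one of them makes the time origin depend on the arm. That is explicit text, not detail left out of a condensed article.

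**Conclusion.** The point holds for the visit-based secondary comparisons: blood and urine markers, echocardiography, biometrics, quality of life, and QALYs if derived from it. Under Treatment and follow-up, the CR arm is assessed systematically later after surgery than the controls, contrary to Secondary outcome measures. The gap is about 0.3 to 2 weeks on the literal reading, resting on an assumed stay of 2 to 14 days. It is 4 to 6 weeks only if randomisation to CR means entry to CR, and the wording does not settle that. The first smoking test has a smaller mismatch of its own, in the opposite direction.

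Whether this would create a false benefit of CR depends on how fast each marker is changing, which the documents do not say. The primary outcomes, the time-to-event outcomes and the general 6-week assessment are untouched. It should be fixed, because the bias is avoidable and the correction cheap, but it does not threaten the main purpose of the pilot.

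**What to change.** Reconcile Treatment and follow-up with Secondary outcome measures:

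1. State one time origin, the same in both arms, for the 12-week and 6-month visits. Randomisation is the natural choice because Secondary outcome measures already uses it. What matters is that it is common to both arms.
2. Delete the separate rules that count the standard-care visits from surgery, and give the 12-week marker assessment an explicit time for controls.
3. Time the first cotinine and carbon monoxide test with the general 6-week assessment in both arms.
4. Leave the general 6-week assessment and the time-to-event outcomes as they are.

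**Cost.** Wording in the protocol, case report form and visit windows; no extra visits. With randomisation as origin, control visits move later by about the post-operative stay (0.3 to 2 weeks as assumed). If CR visits are currently booked from entry to CR, they move earlier by 4 − 2 = 2 to 6 − 0.3 = 5.7 weeks.

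There is one real downside. CR starting 4 to 6 weeks after repair and lasting 8 to 12 weeks ends 12 to 18 weeks after surgery, whereas a 12-week visit counted from randomisation falls at about 12.3 to 14 weeks. Some patients would be assessed before finishing CR, as they already would be on the literal reading of the current text. The sponsor should accept this openly when choosing the common origin.

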## Discussion

Given that this study straddles specialties, particularly cardiology and vascular surgery, an extensive collaborative approach has been employed to the benefit of the study design and patient pathway. Pragmatically, rather than trying to standardise the cardiac rehabilitation (CR) received by patients not only at the two sites, but also at individual CR locations within those sites, we have adopted the view that the existing programmes at each venue will be followed. National CR guidelines are already in place.

An electronic Case Report Form (CRF) has been developed in conjunction with the Kings College Clinical Trials (KCTU) unit to ensure consistency in data inputting and to streamline the analysis of results. This will also allow assessment of the practicalities of using such an electronic database across multiple sites. Randomisation will be carried out electronically using an online randomisation tool developed by KCTU that is accessible at both sites. A Trial Manager has been appointed to oversee the study, based at St George’s.

## Trial status

This trial commenced recruiting patients in September 2014 at both sites.

## Abbreviations

A/TAA: Abdominal aortic aneurysm
ABPI: Ankle-brachial pressure index
BMI: Body mass index
BNP: Brain natriuretic protein
CR: Cardiac rehabilitation
CRF: Case report form
eGFR: Estimated glomerular filtration rate
EVAR: Endovascular aneurysm repair
EQ5D5L: EuroQol questionnaire
GP: General practitioner
HBA1C: Glycosylated haemoglobin
HTA: Health technology assessment
hsCRP: Highly sensitive C-reactive protein
KCTU: King’s clinical trials unit
NICE: National Institute for Health and Care Excellence
NIHR: National Institute for Health Research
TAA: Thoracic aortic aneurysm
